### Setting

This trial will be undertaken at a single NHS site, North East London NHS Foundation Trust in the acute mental health inpatient services.

### Sample size

We will aim to recruit sixty participants in line with recommendations by Consolidated Standards of Reporting Trials (CONSORT) for feasibility and pilot RCTs [13], thirty of which will be randomly allocated to the therapy arm and thirty to the TAU arm. A sample of sixty is deemed of sufficient size to examine the aims of the study. Data (relevant means and standard deviations) from this study will be used to inform a power calculation for a future larger multi-site trial. The sample size will also allow for dropouts, which are common in clinical trials in acute mental health inpatient settings. Some studies report attrition rates of over 50% [36], and recruiting a larger sample will still allow us to collect adequate data to inform a larger multi-site trial.

### Participants

Purposive sampling will be conducted to ensure that the sample is representative of the service user population, with at least 50% from ethnic minority backgrounds and at least 30% of the total sample from Black ethnic backgrounds.

Inclusion criteria for participants will be (i) aged 18 and above; (ii) who meet criteria for a schizophrenia-spectrum diagnoses (schizophrenia, schizophreniform disorder, schizoaffective disorder, delusional disorder or psychotic disorder not otherwise specified; ICD-10), or meet criteria for an early intervention service (EIS) for treatment of psychosis to allow for diagnostic uncertainty; (iii) able to give informed consent and have the capacity to consent; (iv) currently receiving care from an acute psychiatric inpatient team; and (v) able to complete the research in English. Exclusion criteria will be (i) non-English speakers (due to translation costs and difficulty of producing valid translations of the research instruments and intervention), (ii) an acquired brain injury or substance misuse judged to be the acute cause of the psychotic experiences and (iii) those already undertaking a structured psychological intervention delivered by a psychologist or trained therapist at the time of the study.

### Randomisation and blinding

The randomisation will be undertaken using www.sealedenvelope.com. Participant numbers will be entered into the sealed-envelope website by an individual independent from the trial after the research assistant has completed the baseline assessment. Allocations will be emailed to the PI who will then contact the therapists to commence therapy with the participants assigned to the intervention arm and inform participants of their allocation.

All assessments will be completed by research assistants who will be blind to treatment allocation. The research assistants will work in a separate team and building with the therapists to minimise blind breaks. The research assistants will be appropriately trained to administer all outcome measures. Blinding will be monitored, and if any blind breaks (i.e. the research assistant being exposed to the participant’s treatment condition) occur, they will be systematically recorded.

### Stakeholder involvement for the development of this protocol

This research protocol was presented at the North Thames Collaborations for Leadership in Applied Health Research and Care (CLAHRC) Patient and Public Involvement (PPI) panel to shape study conception and research design (twice in 2018). The panel supported the aims of this project and thought the outlined methodological design was appropriate and recommended the development of a stakeholder consultation group who are consulted throughout the duration of the research study (particularly during the intervention development). The panel also gave some initial feedback on the core components of the intervention which were all integrated into the therapy protocol.

### Stakeholder involvement for this research study

A stakeholder group of eleven experts (service users, family/carers, inpatient clinicians and researchers) was convened in August 2020 to contribute to key decisions about the design of the intervention and research trial and was informed of coproduction principles outlined by INVOLVE [18] and the National Survivor User Network [32] 4pi framework. Recruitment for the panel was conducted through the McPin Foundation and the Mental Health Policy Research Unit (MHPRU) respectively for service user and carer stakeholders, and through social media and the professional network of the lead researcher respectively for mental health inpatient staff and researchers. Purposive recruitment of stakeholders was undertaken to ensure there was diversity within the group. Meetings were conducted every month whilst the intervention was being developed and will continue at quarterly intervals for the duration of the trial. Six stakeholder meetings have been undertaken to date (August to January 2020) and have focused on the adaptions to the CBTp intervention including identifying the key underlying values and principles, delivery format, crisis priorities for service users and carers, how to include family/social networks, culturally appropriate adaptations (e.g. including religious spiritual and community understanding and support into the intervention) and ensuring cultural sensitivity. To date, all meetings have been conducted remotely due to COVID-19.

### Study arms

Participants will be randomised to one of two conditions: the crisis-focused CBTp intervention arm or the treatment as usual arm.

#### Crisis-focused CBTp intervention

The trial intervention will be delivered by psychological therapists working in the acute inpatient services. All therapists are clinical psychologists or counselling psychologists registered with the UK Health and Care Professions Council [HCPC], with experience of delivering CBTp in inpatient settings.

The crisis-focused CBTp intervention is underpinned by a modularised CBTp protocol that aims to deliver approximately six to eight sessions of therapy to participants. The protocol includes seven modules; engagement, assessment and identifying priorities; formulation of the crisis; stabilisation and safety; coping, self-management and problem solving; crisis plans and crisis cards; change strategy work focusing on crisis appraisals and safety behaviours; and discharge, relapse planning and recovery toolkits. The first two modules (engagement, assessment and identifying priorities, and formulating the crisis) are essential components of the intervention and the remaining ones are collaboratively chosen based on the participant’s priorities. The number of sessions will be determined by the collaborative priorities set by the service user and therapist and the length of admission, and therefore, more or less sessions can be offered. The therapy will also include at least one follow-up session post-discharge to ensure support through the discharge process. The intervention will also include strategies to involve the individual’s network, e.g. family sessions, and formulation sharing with the multi-disciplinary team.

The sessions will be delivered in a private and quiet room on the inpatient ward or outside/off the ward if the participant has the appropriate leave, e.g. in a room off the ward but on the grounds of the hospital. If the participant is discharged before therapy is complete, the sessions will continue and be delivered in community settings or remotely (e.g. via phone or video conferencing technology). This is to ensure that there is continuity in sessions post-discharge.

##### Training and supervision of the therapists

The therapists received a training package which involved watching pre-recorded therapy videos (https://www.psychosisresearch.com/cbt-phase-1/), and 2 days of training specifically focusing on crisis-focused CBTp. The training, delivered by LW, CW and a service user with lived experience of therapy and inpatient care, comprised an introduction to the crisis-focused CBTp model, making culturally appropriate adaptations, undertaking a crisis-focused assessment, developing a crisis-focused formulation and utilising brief crisis-focused intervention strategies. It included a combination of didactic teaching, role plays, reflective exercises and group discussion. They will also have access to weekly 90-min group supervision whilst delivering the therapeutic intervention.

##### Fidelity to therapy

All therapy sessions will be audio recorded, if the participants consent. Ten percent will be rated on the Cognitive Therapy Rating Scale [5] to ensure adherence to the CBT model. Some adaptations to the application of the fidelity scale will be made, taking into account that the therapy is being delivered as a brief intervention and with people in an acute mental health inpatient population, which may make some of the fidelity items harder to achieve. For example, the agenda may only be brief and only include a single agenda item, specific thoughts/cognitions may not always be identifiable, and only a simple formulation may be possible (making basic links between thoughts, feelings and behaviours).

##### Monitoring what is delivered

The therapists will record the content and delivery of the sessions, including information on the session length, agenda and types of CBTp strategies utilised (e.g. assessment, formulation, relapse prevention) on a pre-defined database.

#### Treatment as usual (TAU)

This will be the routine care that participants receive within the acute inpatient setting. This includes multi-disciplinary care from mental health nurses, nursing assistants, psychiatrists, pharmacists, occupational therapists and psychologists. TAU will include access to routinely delivered psychosocial intervention; this can include structured psychological therapies delivered by clinical or counselling psychologists and brief interventions delivered by appropriately trained nurses or occupational therapists. The NHS study site employs a maximum of 0.4 whole time equivalent (WTE) of a qualified psychologist (clinical or counselling) and 0.8 WTE of an assistant psychologist input per 20 acute care beds. The trial therapists also work in treatment as usual; however, recruitment will not be conducted on the ward in which they are offering treatment as usual so it is extremely unlikely study participants will be offered therapy from the trial therapists. They will also not use any of the therapy resources in treatment as usual.

### Procedure

Participants will be recruited from three male acute wards, three female acute wards, three acute wards for older adults and one male psychiatric intensive care unit (PICU) in North East London NHS Foundation Trust (NELFT). The study will be advertised to the inpatient staff teams who will in turn provide information about the study to eligible participants. Due to the high turnover in acute mental health inpatient wards, inpatient staff will advertise the research to service users as early as the first day on the ward, if appropriate to do so. If participants consent, they will be contacted by a research assistant within 72 h who will share more detailed information and gain informed consent if the service user wants to participate. The research assistant will undertake all clinician-administered and self-report measures with the participant (see Table 1). Once complete, the research assistant will inform the PI of the participant number who will randomise the participant to either the CBTp intervention or TAU. The PI will inform the participant of their allocation. The research assistant will then complete further assessment sessions with all participants at 2 months post-randomisation and 6 months post-randomisation. Relapse, rehospitalisation, and adverse event data will be collected at 12 months, which does not involve contact with the participant.

### Outcomes

#### Feasibility outcomes

Individual patient data will be collected on a pre-developed sheet adhering to CONSORT guidelines [6, 39]. This will include the patient eligibility status, number of referrals received by ward staff, willingness of participants to consent, willingness of participants to be randomised and attrition. Therapy-specific data will include the number of sessions attended, number of sessions declined or not attended, number of people who declined therapy once randomised, therapy resources used, mode of therapy, location of therapy sessions, number of sessions conducted prior to and post-discharge, time and duration of sessions, quantity of homework completed and any serious adverse events. Patient outcome measure completion will also be examined.

An individual patient demographics sheet will be used to collect sociodemographic and service user data, in order to identify the types of people willing to take part in such a trial.

#### Clinical outcomes

Clinical outcome measures will be completed by a research assistant blind to treatment allocation. In order to reduce participant burden, a combination of self-report outcomes, assessor-rated outcomes and a structured clinical interview has been chosen. The measures will be administered during a face-to-face, or if not possible remote, interview between the participant and the research assistant. Where possible, short versions or sub-components of the measures have been chosen for the same reason.

##### Semi-structured clinical interview

Experiences of psychosis will be measured by the Positive and Negative Syndrome Scale (PANSS) [23]. The PANSS is a frequently used measure of psychosis and has three subscales of positive symptoms, negative symptoms and general pathology. Only the positive subscale will be used to measure positive symptoms. It is a 7-item subscale which will be completed by trained research assistants. Participants can score from 1 (absent) to 7 (extreme) on each item. It has good internal consistency (Cronbach’s *α* = .73) and inter-rater reliability (between 0.83 and 0.87).

##### Self-report outcome measures (to be completed with assistance from the researcher)

Depression will be measured by the Beck Depression Inventory brief 7-item measure (BDI-7 [3]). This is a self-report measure which has good internal consistency. Participants can score from 0 (not present) to 3 (indicating severe) and have a total score of 21. Items examine symptoms of sadness, pessimism, past failure, loss of pleasure, self-dislike, self-criticism and suicidal thoughts. It has good internal consistency (Cronbach’s *α* = .86).Hopelessness will be measured by the short-form of the Beck Hopelessness Scale (BHS; [2]), which is a recently developed 9-item version of the scale validated for psychiatric inpatients [1]. The 9-item measure includes items 2, 6, 11, 12, 14, 16, 17, 18 and 20 from the original scale. Participants can score 0 (not present) or 1 (present) on each item. Items include “My future seems dark to me” and “I have great faith in the future”. The 9-item version has good internal consistency (Cronbach’s *α* = .86).Personal recovery will be measured by the 15-item Process of Recovery Questionnaire (QPR; [25]). Participants can score from 0 (disagree strongly) to 4 (agree strongly) on each item and score a total maximum of 40 on the scale. Items include “I feel better about myself” and “I feel that my life has a purpose”. It has good internal consistency (Cronbach’s *α* = .93).Anxiety will be measured on the Generalised Anxiety Disorder-7 item (GAD-7) [44] measure. Participants can score from 0 (not at all) to 3 (nearly every day) on each item. A potential total score can range from 0 to 21. It has good internal consistency (Cronbach’s *α* = .92).Subjective experiences of crisis in psychosis will be examined using a newly developed measure ([name] et al, unpublished). This is a 23-item measure which includes statements such as “I have been feeling very strong distressing emotions” and “I feel able to live my life in line with my morals and values” with scores of between 1 (not at all) and 5 (all of the time) on each item. Participants can score a total of 115. This is not yet validated but its psychometric properties will be examined using study data.Quality of life will be measured by the Recovering Quality of Life (REQOL-10; [23]). Participants rate their quality of life on 10 items from 0 to 4. A participant can score a total of 40. Example items include “I felt lonely” and “I felt happy”. Internal consistency is high (Cronbach *α* = .89).Service use will also be assessed using an adapted version of the “generic UK mental health” version of the Client Service Receipt Inventory (CSRI; [4]). This has been adapted to reflect the local care pathways in the recruitment site. This will be completed through participant self-report and information from clinical notes.

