
##### Clinician/researcher-rated measures

Functioning will be assessed on the Global Assessment of Functioning (GAF) measure [16, 35]. GAF scores range from 1 (in some danger of hurting self or others) to 100 (absent or minimal symptoms), examining both symptoms and functioning. It has demonstrated good internal consistency (Cronbach’s *α* = .80).The Threshold Assessment Grid (TAG) examines the severity of participants’ mental health difficulties [43]. It has seven domains measuring three areas of safety, risk and needs and disabilities. Participants can score from 0 (none) to 4 (very severe) on each domain, which is analysed individually/as a total score. It has good internal consistency (Cronbach’s *α* = .70).

Participants’ clinical records will be examined to gather information on:Hospitalisation: Total number of days in hospital and number of incidentsRelapse: Total days under the care of acute mental health services (including inpatient wards, crisis home treatment, psychiatric liaison and acute crisis and assessment teams) and number of incidentsNumber of serious incidents and adverse events, including those of harm to self and others

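### The blinded rater of PANSS-P, GAF and TAG also completes the service-use inventory from self-report and clinical notes, an avoidable risk of unblinding the follow-up ratings

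*Protocol article*

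**What the plan says.** On blinding, the section Randomisation and blinding states: "All assessments will be completed by research assistants who will be blind to treatment allocation". The section Clinical outcomes repeats the commitment: "Clinical outcome measures will be completed by a research assistant blind to treatment allocation". Two safeguards are given. The assistants are housed apart from the therapists, in a different team and building, and blind breaks are monitored: "they will be systematically recorded".

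On the rated measures, the article says of the PANSS positive subscale: "It is a 7-item subscale which will be completed by trained research assistants". GAF and TAG appear under the heading for clinician- or researcher-rated measures. The Procedure section gives the research assistant both the clinician-administered and the self-report instruments, and has the assistant carry out the 2- and 6-month sessions.

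On service use, the CSRI is listed among the self-report measures completed with the researcher's help, with two sources: "This will be completed through participant self-report and information from clinical notes".

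On what might be visible, the section on the CBTp intervention describes sessions on or near the ward, possible family sessions, "formulation sharing with the multi-disciplinary team", and at least one session after discharge. The PI tells participants their allocation.

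**The concern.** A service-use inventory asks what care a person has received. In this trial the experimental treatment is itself a form of care, delivered within the service whose notes are consulted. Giving that inventory and those notes to the person who must stay blind puts the information the blind protects in front of the rater.

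PANSS-P, GAF and TAG depend on rater judgement, so knowledge of the arm can shift scores. The trial is not powered for effectiveness, so no efficacy claim is at stake. But it sets out to judge whether the measures suit a full RCT, to supply means and standard deviations for that trial's power calculation, and to rehearse the between-arm comparison. Rater bias would carry into the arm means and the rehearsed comparison. The log of blind breaks would also be harder to interpret, because some breaks would come from the data-collection procedure and not from the setting.

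**Working it through.** The article gives no figure for blinding, so the check is a comparison of its sections.

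1. **Who rates.** Research assistants, blind to allocation (Randomisation and blinding; Clinical outcomes; Semi-structured clinical interview). GAF and TAG fall under the same general statement.

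2. **Who completes the CSRI.** It is one of the clinical outcome measures, which the blinded assistant completes, and it sits under the heading for measures done with the researcher's assistance. No other person is named for it. It is absent from Table 1, but so is the quality-of-life measure REQOL-10, so absence from the table does not show that it is handled separately.

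3. **What the assistant is exposed to.** There are two sources. By self-report, participants know their arm because the PI informs them, so questions about services used invite disclosure whatever the notes contain. In the notes, formulations are shared with the ward team and therapy continues after discharge, so an entry is plausible, though the article does not say that one is made.

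4. **Which ratings are at risk.**
   - Baseline: none. Randomisation follows completion of the baseline assessment.
   - 2 months: at risk if the CSRI or the notes come before the ratings. The order is not stated.
   - 6 months: at risk on the same ground, and also if the same assistant saw the notes or heard the CSRI answers at 2 months. The article does not say whether the same assistant returns.

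5. **Whether the safeguards cover this route.** Separate team and building limits contact with therapists. It does not limit contact with notes or with participants' answers. Recording a break documents it afterwards.

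6. **Size.** The target for the CBTp arm is 30 (Sample size). The retention criterion at 2 months is 75% (Feasibility criteria). 0.75 × 30 = 22.5, about 23 participants seen. This counts people seen, not raters unblinded. It is a ceiling at that retention, and it assumes that the CSRI is completed at 2 months. With full retention the ceiling would be 30. The article gives no probability of disclosure, so no expected number follows.

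**The case against.** The strongest reply is that the article does not say what the notes or the adapted CSRI record about trial therapy. Session content goes into a separate therapists' database, and nothing says that shared formulations are filed in the notes. Usual care can include structured therapy from a psychologist, so a psychology contact does not by itself identify the arm. The CSRI sentence is passive and names no one for the notes, and the same holds for hospitalisation, relapse and adverse events, where the article says only that "clinical records will be examined to gather information on". Order of tasks at a visit is working detail that a journal article may leave out.

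Much of this stands, and it rules out stronger readings. A reader might infer that the notes show who receives CBTp, that the follow-up ratings would be made by unblinded raters, or that some 23 participants would be unblinded. The documents support none of these. Nor do they support a prediction that the pilot will report blinding as infeasible, as the feasibility criteria contain no blinding item.

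What the reply does not remove is the stated assignment. The point does not rest on silence: the article gives the blinded assistant the clinical outcome measures, places the CSRI among them and names its sources. Therapy in usual care weakens the signal but does not erase it. Recruitment avoids the wards where trial therapists give usual care, so a rater who recognised a trial therapist's name in a record would have a strong clue to the arm. Usual-care psychology is limited to at most 0.4 whole-time equivalent of a qualified psychologist per 20 beds, and people already in structured therapy are excluded. Disclosure by self-report needs no notes at all.

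**Conclusion.** The point holds as a risk, not as a certainty. As written, the blinded rater of PANSS-P, GAF and TAG also completes a service-use inventory from self-report and clinical notes, and neither stated safeguard covers that route. Three rater-judged outcomes at up to two follow-up times are exposed.

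The conclusion assumes that the CSRI is completed by the research assistant, as the general statement on clinical outcome measures implies. For 2 months it further assumes that the CSRI or the notes precede the ratings. For carry-over to 6 months it assumes that the same assistant returns. If a fuller protocol already orders the tasks or names another extractor, the risk is met and the article needs only to say so. The change is worth making because it is cheap and because protecting the rated outcomes is part of what the pilot is testing.

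**What to change.** - At each follow-up visit, score PANSS-P, GAF and TAG before any service-use question is asked.
- Have the notes-based CSRI data, and all items on psychological-therapy contact, collected by someone other than the rater or after that participant's 6-month rating. Cover trial and usual-care therapy alike, in both arms.
- Keep the therapy items. The therapists' database is described only for trial sessions, so dropping them could lose usual-care therapy and make capture differ between arms.
- State who extracts hospitalisation, relapse and adverse-event data, and keep that work away from a rater with ratings still to make for that participant.

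The cost is wording and order of tasks. Sample, measures and visits do not change. Some service-use data will arrive later, or another existing team member will collect them. If that person knows the allocation, use the same extraction form and rules in both arms, so that the bias is not moved from the ratings to the record-based outcomes.
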